### Reimbursement

Upon completion of the final questionnaire and return of any project materials, participants are thanked for their participation and receive a $50 Gift Card as reimbursement for their involvement and time. Following their completion, participants receive a comprehensive list of relevant perinatal support services and organisations for further reference.

### Trial Status

The project began recruiting in October 2018 and data collection is ongoing.

## Data Analysis

### Sample Size and Power

Assuming 5% missing data at T0, 10% missing data at T2, and 15% missing data at T3 (53), a sample size of 90 powered adequately at 82% (two tailed α = 0.05) to detect a medium effect size (*f* = 0.25), which was observed in a recent CBT for insomnia trial on prenatal insomnia (22).

### Data Storage and Management

All data collected are stored using password protection. Participants' personal details are stored separately from responses to questionnaires and telephone interviews and are only accessible to primary investigators and research assistants. Only primary investigators will have access to questionnaire responses and the final dataset. All identifiable information is kept for 7 years following arising publications and will be destroyed after this point.

To promote data quality, data will be screened for accuracy and further enquiries are made and rectified. Participants are encouraged to request further clarification of questionnaire items if unsure and are provided with assistance via email or telephone by the lead researcher (SV). Results will be analysed upon completion of the trial once all data have been collected. Participants are assigned a unique alphanumeric code which is used to link data across time-points. No data monitoring committee will be employed in the current trial due to limited scale, nor will trial auditing be undertaken.

### Statistical Analysis

All analyses will be conducted on an intention-to-treat basis and will be analysed using R (48) and Mplus (77). Missing data is expected in a longitudinal design and will be addressed using full information maximum likelihood in the structural equation modeling framework (78). Descriptive statistics will be used to characterize baseline demographic characteristics, rates of missing data over time and outcomes over time. Exploratory analyses and graphs will be used to identify univariate or multivariate outliers as well as to evaluate normality assumptions for primary and secondary analyses. Extreme outliers will be winsorised.

Primary and secondary outcomes will be examined using latent growth models. Piecewise models will be used to allow different rates of change: from baseline (T0), through mid-point (T2), to immediate post-intervention (T3) called Slope 1, and from immediate post-intervention (T3) to one-month follow-up (T4) called Slope 2. Loadings for Slope 1 will be 0 for T0 (fixed), freely estimated for T2, 1 for T3 (fixed), and 1 for T4 (fixed). Loadings for Slope 2 will be fixed at 0 for T0, T2, and T3 and fixed at 1 for T4. This model is saturated for the outcome means at each timepoint to ensure that change over time is accurately modeled. The primary trial endpoint for all outcomes is Slope 1, which captures change from baseline to post-intervention. Slope 2 captures maintenance of treatment results over the one-month follow-up and is an exploratory endpoint. The residual variance will be constrained to be equal across time (homogenous) and independent (i.e., an independent, homogenous residual structure). Intercepts of manifest variables for the outcomes will be constrained to 0 to allow estimation of the latent random intercept mean. The intercept and Slope 1 variances and covariances will be freely estimated. The variance of Slope 2 and its covariance with the intercept and Slope 1 will be freely estimated if possible, but given it comprises only two timepoints, if there are convergence or estimation problems, the variance of Slope 2 will be constrained to 0. The two stratification factors, ISI (≤ 14 and >14) and infant age (<8 and ≥8 months) will form four grouping conditions: Early Postpartum Low ISI, Late Postpartum Low ISI, Early Postpartum High ISI, and Late Postpartum High ISI. Dummy codes will be created for each, with Early Postpartum Low ISI as the reference group. These dummy codes will be included as covariates to adjust for effect on the random intercept (79, 80).

Two “treatment” variables (one on the presence/absence of CBT, the other presence/absence of LDT) will be included in the models to predict the intercept, and slopes of each piece, with treatment factors constrained to 0 for the intercept to implement “constrained longitudinal data analysis,” which provides a more accurate estimate of treatment effects from RCT with repeated measures (81, 82). This tests whether the change in outcomes over time (from baseline through mid-point to post-intervention) is different with the presence/absence of CBT or LDT. Effect sizes of the group difference at each time point also will be calculated as adjusted, standardized mean differences by taking the model estimated difference between groups at each time point and standardizing by the combined residual and random intercept variance. A robust maximum likelihood estimator, which is robust to non-normal data (83), will be used to derive confidence intervals and statistical inference. Given this and to maintain interpretability of results, outcomes will be transformed only if visual inspection indicates significant departures from normality.

Sensitivity analyses will be conducted replicating the primary analyses but including receipt of sleep interventions (e.g., starting sleep medication/therapy) outside of the study as a covariate to examine whether this alters study results. To explore predictors and mediators of intervention effects (e.g., changes in sleep-related beliefs, social support, treatment adherence), regression, mediation, and moderation analyses will be conducted. The authors may be contacted regarding access to full trial protocol, intervention materials, and statistical code.

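### Once treatment is added, the growth model is no longer saturated for the arm means: the mid-point effects are tied to the post-intervention effects, and the primary Slope 1 effect can be biased if arms improve at different tempos

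*Protocol article*

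**What the plan says.** All of this is in the Statistical Analysis section of the protocol article.

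- Slope 1 shape: "Loadings for Slope 1 will be 0 for T0 (fixed), freely estimated for T2, 1 for T3 (fixed), and 1 for T4 (fixed".
- Slope 2 shape: "Loadings for Slope 2 will be fixed at 0 for T0, T2, and T3 and fixed at 1 for T4".
- Saturation: "This model is saturated for the outcome means at each timepoint to ensure that change over time is accurately modeled". The sentence does not mention arms, and it comes before the treatment variables are introduced.
- Primary endpoint: "The primary trial endpoint for all outcomes is Slope 1, which captures change from baseline to post-intervention".
- Treatment: the CBT and LDT indicators "will be included in the models to predict the intercept, and slopes of each piece", "with treatment factors constrained to 0 for the intercept". The text describes no direct path from treatment to the T2 outcome, no arm-specific loading and no multi-group model.
- Reporting: "Effect sizes of the group difference at each time point also will be calculated as adjusted, standardized mean differences", taken from the model.

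The stratum dummies act on the intercept only, so they add no freedom to the arm means at T2.

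**The concern.** Saturation is offered as the guarantee that change over time is modelled accurately. A reader will carry that guarantee over to the treatment comparison, all the more because the section goes on to invoke constrained longitudinal data analysis. In its usual form, that method leaves the post-baseline arm means free. Here they are not free at T2.

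Two things are at stake. The T2 effect sizes would be reported as estimates although they are a fixed fraction of the T3 effects. And T2 data that do not fit the fraction can pull the Slope 1 effect, the primary endpoint for every outcome, away from the true difference in change from baseline to T3.

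Different tempos are plausible. The arms differ in mechanism and delivery: CBT content is spread over six weeks, LDT uses light every morning, and TAU receives no intervention. Entry requires an ISI of at least 8, so some early improvement in TAU may be regression to the mean. The protocol gives no reason to expect one common time course.

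**Working it through.** The plan gives no figure on this point to reproduce. Its 82% power does not enter.

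**Step 1: implied means.** Let m0, a and b be the means of the intercept, Slope 1 and Slope 2; λ the free T2 loading; and c and d an arm's effects on Slope 1 and Slope 2 (both 0 for TAU). Then:

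- T0: m0
- T2: m0 + λ(a + c)
- T3: m0 + a + c
- T4: m0 + a + c + b + d

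Arm minus TAU is λc at T2, c at T3 and c + d at T4. T4 is free because of d; T2 is not. The same λ fixes the T2 effect of both CBT and LDT, TAU's own course (λa), and part of the covariance matrix.

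**Step 2: count.**

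- Plan: m0, a, b, λ, two c and two d = 8.
- Free arm means with a common baseline: 1 + 3 × 3 = 10.
- The numerical rank of the arm-by-time means in these parameters is 8, so there are two restrictions, one per active arm.
- The four pooled means have rank 4, so by count the saturation sentence is right for them.

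**Step 3: consequence for Slope 1.** The plan's model was fitted by maximum likelihood to exact (large-sample) arm means, with complete data and no strata. *All inputs are assumptions*: the protocol gives no ISI standard deviation, correlation or trajectory.

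The base covariance has intercept variance 12, Slope 1 variance 10, their covariance -2, Slope 2 variance 2, residual variance 6 and T2 loading 0.5. This gives a baseline SD of √18 = 4.24, a T3 SD of √24 = 4.90 and a T0–T3 correlation of 10/√(18 × 24) = 0.48. Except in the last two rows, the baseline mean is 14, TAU change is -2, and the true T3 effects are -4 (CBT) and -3 (LDT). The fractions are the share of each arm's own T0–T3 change reached by T2.

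| Assumed course | Bias in Slope 1 effect, CBT / LDT (ISI points) |
|---|---|
| Same fraction in all arms | 0.00 / 0.00 |
| CBT 0.3, others 0.5 | +0.04 / -0.01 |
| CBT 0.8, others 0.5 | -0.37 / +0.13 |
| CBT 0.8, LDT 0.3, TAU 0.5 | -0.36 / +0.31 |
| CBT and LDT 0.9, TAU 0.3 | -0.65 / -0.61 |
| CBT effect -2 at T2, 0 at T3; TAU and LDT 14, 13, 12, 12 | -0.68 / 0.00 |
| CBT effect 0 at T2, -3 at T3; TAU and LDT 14.1, 11.7, 11.1, 11.1 | +0.30 / 0.00 |

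With other assumed covariances and TAU courses, the transient case gave Slope 1 effects of about -0.4 to -1.0 (truth 0). The late case gave about -2.6 to -3.1 (truth -3).

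**Step 4: consequence for the T2 effect sizes.** In the transient base case λ = 0.694, so the model's T2 effect is 0.694 × (-0.683) = -0.47 against a true -2. In the late base case it is 0.528 × (-2.704) = -1.43 against a true 0.

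**Step 5: scale.** The standard error of a T3 contrast with 30 per arm is √[(24 - 10²/18) × 2/30] = 1.11, so a bias of 0.68 is about 0.6 standard errors. With 30 per arm, complete data and 400 replicates, the transient case gave a mean estimate of -0.62 and 13.8% rejection by a 5% likelihood-ratio test. With no effect at any time the mean was 0.01 and rejection 6.0%.

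**The case against.** The strongest reply has four parts.

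1. *The sentence is correct as written.* It speaks of outcome means at each time point, before treatment enters, and those four means are just-identified by count. This stands. A reader might infer that the plan makes a false claim about arm means, but the text never mentions arms. The valid criticism is that the property does not carry over to the model with treatment.

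2. *The bias is conditional.* This stands too. A reader might infer that Slope 1 is biased as such, or that a late effect loses about a quarter of its size. The documents do not support either. Bias needs arms of different shape, it can go either way, and a moderately late CBT effect moved the estimate by only 0.04. An attenuation as large as a quarter was not borne out when the late case was refitted under a range of assumptions.

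3. *The CBT schedule is not late.* The protocol sends 5 + 4 + 3 = 12 of 21 emails (57%) in Weeks 1 to 3 and places a 60-minute orientation call in Week 1. A zero CBT effect at Week 3 is therefore an extreme case. This weakens the late scenario but does not make the three arms share one tempo.

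4. *The test is described as covering change through the mid-point,* so a mid-point difference is partly within the hypothesis, and the 13.8% is not a type I error rate under no effect at all. That is fair. But the endpoint is defined as change from baseline to post-intervention, and a difference gone by T3 is not such a change.

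**Conclusion.** The restriction is certain. It follows from the loadings and treatment paths as written: 8 mean parameters against 10, with both T2 effects tied to their T3 effects by one λ. The T2 effect sizes carry it directly.

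Bias in the primary Slope 1 effect is possible, not established. It is nil with a common shape or with no effect at any time. Otherwise it ran from about 0.01 to 1.0 ISI points, in either direction, under the assumed values. The size rests on assumed means, standard deviations and correlations, and on fits without missing data or stratum covariates. The count does not depend on any of these.

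**What to change.** Free the T2 arm means in the primary model, in one of two ways:

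- **Categorical-time constrained longitudinal analysis:** a common T0 mean, separate arm means at T2, T3 and T4, and arm minus TAU at T3 as the primary contrast. The fitted means then carry no such restriction.
- **Keep the growth model** and add a direct path from each treatment variable to the T2 outcome. This brings the count to 10 and removes most of the bias. Because λ also shapes the covariance, a remainder of roughly 0.1 points can persist: it was 0.00 to 0.05 in most refits, and up to about 0.16 in the late case, where TAU's mean course and the covariance implied different loadings.

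Limit the saturation sentence to the model without treatment, or delete it.

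The cost is two more mean parameters, plus more covariance parameters if an unstructured matrix is used. Little loss of power is expected: in one simulation with an effect proportional over time (N = 90, with 10%, 15% and 18% missing at T2, T3 and T4), power was 55% with free means and 53% with the plan's model. The protocol reports data collection as ongoing and analysis only after completion, so the change can be specified in advance.

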### Participants

Inclusion criteria are: (a) nulliparous women (i.e., first-time mothers with no older children) 4–12 months postpartum; (b) age ≥18 years; (c) reports symptoms of insomnia, operationalised as scoring ≥8 (subthreshold insomnia) on the Insomnia Severity Index [ISI; (44)]; (d) singleton pregnancy; (e) ability to read and write in English; (f) regular access to telephone, email and the internet. Nulliparous women were chosen given the higher risk of poorer sleep compared to multipara (2, 45, 46).

Exclusion criteria are: (a) current pregnancy; (b) night shift work; (c) current severe or untreated sleep disorders (e.g., narcolepsy, sleep apnea, restless legs syndrome, circadian rhythm disorders); (d) take medications or have medical conditions that directly affect sleep (e.g., sleep medication, antidepressants); (e) report current severe psychopathology (e.g., bipolar disorder, post-traumatic stress disorder) or are at high risk of harm to self/others; (f) have infants with medical conditions that affect sleep; (g) suffer from epilepsy; (h) report photosensitivity or have been recommended by health professional to avoid bright light; (i) report current unsettled infant sleep behaviour, operationalised as infant waking on average >3 times per night and requiring parental assistance to reinitiate sleep; this final exclusion criterion was established as this trial focuses on the management of maternal insomnia symptoms rather than sleep deprivation primarily due to infant care. Participants are permitted to receive ongoing usual care for physical and/or mental health conditions.

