#### Randomisation and Blinding

Eligible participants are randomised using a complete randomisation scheme generated in advance. Specifically, block sizes of variable size (3, 6, 9) are used. Random seeds are generated to assure allocation concealment and pre-guessing of the allocation sequence at the end of each block. Randomisation are stratified by baseline ISI (≤ 14 and >14) and infant age (<8 months and ≥8 months). As noted on trial registration, this protocol commenced as a four-arm trial with the fourth arm receiving both CBT and LDT. Due to significant and unexpected changes in the first author's personal circumstances during the early phase of this trial, this fourth arm was removed after 31 participants were randomised (9 to the removed condition) to ensure timely trial completion. Randomisation used during this initial phase was identical to subsequent 3-arm randomisation described above, except the randomisation scheme had block sizes of 4 or 8.

The randomisation scheme is generated in R (48) and is set up in REDCap by a member of the research staff who is not involved in recruitment or delivery of intervention and not a principal investigators. To randomise a participant, an authorised research staff member logs into REDCap, enters eligibility and participant stratification data before receiving group allocation. Participants are not blinded but are asked to withhold group allocation from research assistants during the post-intervention telephone call.

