### Interventions

All participants, regardless of group allocation, continue usual postpartum care. No participants are restrained from seeking treatment or support for sleep concerns. Treatment or support received outside of the study interventions are documented.

Interventions include therapist-assisted and self-directed/automated components which are delivered via distance. Interventions are manualised and telephone scripts were developed by the research team to ensure consistency. A provisional psychologist undertaking doctoral training in clinical psychology (SV) who was trained prior to trial commencement in CBT for insomnia delivery by a clinical psychologist (BB) carries out intervention telephone calls and receives regular supervision throughout the trial.

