#### Cognitive Behavioural Therapy

The CBT material is based on CBT for insomnia adapted for perinatal populations (22, 50). This mode of treatment has been identified as the intervention of choice by pregnant women and their partners compared to pharmacotherapy and no treatment (51). To adapt intervention for later postpartum months, a focus group with four new mothers was carried out to aid intervention development and provided guidance on content and delivery format. Strategies are delivered via emails which are designed to be visually-attractive, easy-to-read and brief (see Supplementary Material), in light of recommendations provided in the focus group. Components of the CBT intervention include: psychoeducation, stimulus control, healthy attitudes and behaviours around sleep, sleep hygiene, relaxation, managing unhelpful thoughts and worries, fatigue management, prioritising rest and self-care, enlisting social support and infant settling. Emails are delivered using an online software that provides professional email templates and automates the timing of intervention delivery based on each woman's own progress. In total, 21 emails are delivered: five in Week 1, four in Week 2, followed by three emails per week in Weeks 3 to Week 6.

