#### Other Factors

Demographic, medical conditions, and obstetric information are collected using self-report at baseline (T1) and changes are monitored at T3 and T4 (e.g., infant-feeding method, medical conditions of mother/infant, engagement in therapy, medication use).Postnatal Sleep Questions include self-reported maternal sleep behaviours over the past week (e.g., sleep duration, onset latency, wake after sleep onset, daytime naps adapted from the Consensus Sleep Diary (63).Self-reported maternal sleep history (i.e., pre-pregnancy sleep) are assessed using adapted versions of the PROMIS-SD-SF and Postnatal Sleep Questions.Maternal mental health, measured with the Cross-Cutting Symptoms Level 1 (64).Mother-infant attachment quality, assessed using the Mother to Infant Bonding Scale (65).Relationship satisfaction with the partner, measured using the brief Dyadic Adjustment Scale – 4 (66).The following are assessed and examined as potential covariates: infant sleep [Brief Infant Sleep Questionnaire; (67)]; perceived stress [Perceived Stress Scale; (68)]; social support measured using the PROMIS Instrumental Support – Short Form – 4a and PROMIS Emotional Support – Short Form – 4a (69); questions on the partner's sleep behaviour and overnight assistance with infant care are also included.Feasibility and acceptability are assessed implicitly via recruitment and dropout rates, and explicitly via the Client Satisfaction Questionnaire (70) and qualitative feedback from participants.Due to ongoing data collection during the COVID-19 pandemic, questions related to personal experiences with COVID-19 and potential impact on participation are asked to all participants who completed the project after mid-February 2020 (shortly before the outbreak was declared a national pandemic in Australia). This is intended to assist with interpreting findings from this trial following completion.

The following constructs will also be measured and explored as predictors or mediators of treatment responses:

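### Adjusting for outside sleep treatment started after randomisation does not give a randomised comparison, so this sensitivity analysis cannot show unambiguously whether outside treatment altered the results

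*Protocol article*

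**What the plan says.** The primary analysis is a piecewise latent growth model, analysed by intention to treat. Its only fixed covariates are dummy codes for the stratification groups. The primary endpoint is Slope 1, the change from T0 to T3. The Statistical Analysis section then adds a sensitivity analysis that repeats this model "including receipt of sleep interventions (e.g., starting sleep medication/therapy) outside of the study as a covariate to examine whether this alters study results".

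Four other places bear on what that covariate is:

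- **Participants** excludes at entry women who "take medications or have medical conditions that directly affect sleep (e.g., sleep medication, antidepressants"). Receipt of sleep medication therefore arises mainly after enrolment.
- **Interventions** states: "No participants are restrained from seeking treatment or support for sleep concerns". It adds that outside treatment is documented, without saying how or when.
- **Randomisation and Blinding** states: "Participants are not blinded but are asked to withhold group allocation from research assistants during the post-intervention telephone call".
- **Other Factors** says of baseline information that "changes are monitored at T3 and T4 (e.g., infant-feeding method, medical conditions of mother/infant, engagement in therapy, medication use").

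The article does not say which growth factor the added covariate would predict, or how a shift in the treatment effect should be read.

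**The concern.** Starting outside treatment is an event during follow-up, not a baseline characteristic. A woman who knows she is in TAU, or whose insomnia persists, is plausibly more likely to seek help. If so, women who start outside treatment differ in prognosis from those who do not, and the mix differs by arm. Conditioning on that event compares groups that randomisation did not create.

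The stated purpose is to see whether outside treatment changes the findings, so what is at stake is how the check is read. A reader who sees the effect shrink may conclude that outside treatment explained part of it. A reader who sees no change may conclude that contamination was negligible. Either conclusion can be wrong.

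**Working it through.** The plan gives no figure to reproduce here, so the check is algebra plus illustration.

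**Inputs from the article.** The covariate, unrestricted outside care, unblinded participants, the T3/T4 change questions, and 90 women randomised 1:1:1 (30 per arm).

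**Inputs assumed.** Uptake by arm, the benefit of outside treatment, and the link between uptake and prognosis. The article gives none of these.

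**Step 1: what adjustment does.** Let p_A and p_T be uptake in an active arm and in TAU. Let g be the within-arm regression coefficient of the outcome on outside treatment. In a linear model without other covariates,

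adjusted effect = total effect − g × (p_A − p_T).

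Here g = b + s. The term b is the true effect of outside treatment (negative if it helps). The term s is the selection part (positive if the women who seek help are doing worse). Adjustment cannot separate b from s.

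**Step 2: SD units.** The assumed direct treatment effect is −0.50. In cases 2 to 4, uptake is 10% active and 30% TAU, so p_A − p_T = −0.20.

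| Case | Total | Adjusted | Shift |
|---|---|---|---|
| 1. Equal uptake, 10% in both arms | about −0.50 | the same | about 0 |
| 2. No outside effect, uptake tracks poor prognosis (correlation 0.5) | −0.500 | −0.379 | +0.121 |
| 3. Outside treatment helps by 0.5 SD, no link with prognosis | −0.396 | −0.496 | −0.100 |
| 4. Both mechanisms | −0.399 | −0.377 | +0.022 |

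These simulated values agree with the formula:

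- Case 2 implies g = s = 0.121 / 0.20 = 0.605. The spurious loss is 0.121 / 0.500 = 24%.
- Case 3 has g = −0.5, so the shift is −(−0.5)(−0.20) = −0.10.
- Case 4 has g = 0.605 − 0.5 = 0.105, so the predicted shift is 0.105 × 0.20 = 0.021.

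In case 4 outside treatment dilutes the effect from −0.50 to −0.40. The check moves by only 0.02, and away from −0.50.

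**Step 3: ISI points.** The true effect is −2.5, outside treatment has no effect, and uptake is driven by Week 3 ISI and arm. Two sets of assumptions were used:

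- First set, uptake 27% TAU and 9% CBT: outside treatment appears harmful by 2.7 points, so −2.51 + 2.7 × 0.18 = −2.02, a loss of 0.49 / 2.51 = 20%.
- First set, uptake 20% and 14%: adjusted −2.36, a loss of 0.15 / 2.51 = 6%.
- Second set, uptake 25% and 9%: apparent harm of 1.5 points, so −2.50 + 1.5 × 0.16 = −2.26, a loss of 0.24 / 2.50 = 10%.
- Second set, uptake 19% and 14%: adjusted −2.43, a loss of 0.07 / 2.50 = 3%.

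**Step 4: closer to the planned model.** A four-timepoint constrained longitudinal model was fitted with the covariate acting on level only. At 27% and 9% uptake the effect goes from −2.45 to −2.24, a loss of 0.21 / 2.45 = 9%. Analysis of covariance on the same data loses 13%. At 20% and 14% the loss is 3%.

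**Range.** With no outside effect and uptake linked to symptoms or prognosis, gaps of 5 to 20 percentage points give losses of about 3 to 24%. A more extreme gap, 5% against 30%, takes −0.493 to −0.341 (0.152 / 0.493 = 31%).

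**The case against.** The strongest reply is that this is a labelled sensitivity analysis. The primary analysis is already intention to treat without this covariate, so the trial's main estimate does not move. That stands and limits the weight of the point. It is also true that every size above rests on assumed uptake, that a model close to the planned one shows smaller shifts than analysis of covariance, and that equal uptake gives essentially none. To say the result cannot be interpreted at all would be too strong. What it lacks is an unambiguous reading.

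Two stronger readings are tempting, and the document supports neither.

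- **Missing covariate.** A reader might infer that about 15% of women would lack the covariate, because Sample Size and Power assumes 15% missing at T3. That figure is missing T3 data. A woman who misses T3 may answer at T4. The risk assessment covers engagement with mental health care and is repeated at the Week 3 call to all participants. Outside treatment is also said to be documented. How many women would lack a value cannot be derived.
- **Other post-baseline covariates.** Other Factors says: "The following are assessed and examined as potential covariates: infant sleep", and goes on to list stress and social support. CBT includes "enlisting social support and infant settling", and the exploratory predictors and mediators include "changes in sleep-related beliefs, social support, treatment adherence". A reader might infer that T2 to T4 values would be adjusted for, removing part of the CBT effect. Nothing says so. All these measures have T0 values, and the only covariates fixed for the treatment models are the stratification dummies and, in the sensitivity analysis, outside treatment.

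**Conclusion.** The point holds for the outside-treatment covariate alone. It is recorded after randomisation, and allocation and prognosis can both affect it, so the adjusted effect mixes any real effect of outside treatment with selection. The estimate can shrink when outside treatment does nothing and stay almost still when it matters. The check therefore does not reliably answer the question it is set.

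The sizes are illustrations. They depend on how far uptake differs by arm and how strongly it follows symptoms, neither of which the article gives. The direction of the argument needs only that both links are possible, and the open-label design with unrestricted care makes them so. The primary estimate stands as planned. The change is worth making before analysis but is of moderate importance.

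**What to change.** 1. Tabulate uptake of outside sleep treatment by arm and assessment. If uptake is rare or similar across arms, that table answers most of the question.
2. Replace the covariate adjustment with a hypothetical-strategy sensitivity analysis. Set outcome scores after the start of outside treatment to missing, and refit the same constrained growth model by the full information maximum likelihood already planned. This estimates a defined quantity: the effect had no outside treatment been started.
3. Take the start from records already held, namely the T3 and T4 change questions and the documented outside treatment, placed to the nearest assessment where no date exists. Fix that rule before analysis. A new start-date question would not cover women who have already finished, because recruitment began in October 2018.

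The cost is analysis-plan wording and some coding of existing records. Two downsides should be stated. First, the analysis assumes that the removed scores are missing at random given the observed ones. Second, it loses later scores, possibly more in TAU. At the assumed 27% and 9% uptake, that is about 0.27 × 30 = 8 women in TAU and 0.09 × 30 = 3 in CBT, in addition to ordinary missing data.
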